### 11.3 Participant Confidentiality

All health-related data will be kept confidential by the investigators involved in this study. Specifically, only the investigators in the study will have access to patient data. Published or presented data will not identify patients in any way. Patients will not be audiotaped or videotaped. Data, forms, reports, and other records that leave the site will be identified only by a participant identification number (Participant ID, PID). All records will be kept in a locked file cabinet. All computer entry and networking programs will be done using PIDs only. Once this research has been completed all files will be kept for an additional five years and then destroyed. Additionally, while every effort will be made to keep study-related information confidential, there may be circumstances where this information must be shared with: 1) Federal agencies, for example the Office of Human Research Protections, whose responsibility is to protect human subjects in research; and 2) Representatives of Ohio University (OU), including the Institutional Review Board, a committee that oversees the research at OU.

### 11.4 Study Discontinuation

This study may be discontinued at any time by the IRB, the NCCIH, the OHRP, the FDA, or other government agencies as part of their duties to ensure that research participants are protected.

## 12. COMMITTEES

**Steering Committee:** The RELIEF Study Steering Committee, which is charged with the overall governance of study conduct, consists of [name], PT, [name], [name], [name] and [name], D.O. The Steering Committee approves the final protocols and manuals of operations, supervises the overall execution of the trial, generates and approves study policies, considers modifications of the protocol and study operations, and plans and drafts study-related publications. The Steering Committee appoints and charges the subcommittees described below. All major scientific decisions are determined by majority vote of the Steering Committee.

**Medical Safety Committee:** The RELIEF Study Medical Safety Committee, which consists of [name], PT, [name], [name], D.O. and Study Coordinator (TBD), reviews masked study data related to the overall safety of study participation, develops safety reports for the Data and

Safety Monitoring Board, addresses IRB issues (related to participant safety) that may arise, reviews clinical practice-related issues and oversees the clinical safety of all study participants.

Data Safety and Monitoring Board: A Data Safety Monitoring Board (DSMB) that consists of an Independent Monitoring Committee IMC (IMC) monitors all aspects of the study, including those that require access to any blinded data.

Recruitment, Adherence, and Retention Committee: The RELIEF Study Recruitment, Adherence and Retention Committee, which consists of the [name], PT, [name], [name], D.O. and members of the Study Coordination and Data Collection Team (TBD), refines and optimizes protocols and strategies for recruitment, adherence and retention of study participants. The Committee oversees recruitment progress, intervenes in cases of under-recruitment, and reports recruitment progress to the Steering Committee.

### **13. PUBLICATION OF RESEARCH FINDINGS**

This study is governed by a Steering Committee and publication of the results of this trial will be governed by the policies and procedures developed by the Steering Committee. Any presentation, abstract, or manuscript will be made available for review by the sponsor and the NCCIH prior to submission.

## Appendix: Supplemental

### Specific Aims

While there is recent evidence that sagittal plane trunk stiffness is greater in men compared to women[65], the role of sex on dynamic trunk stiffness in LBP populations is unknown. Nor it is known if changes in trunk stiffness following spinal manipulative therapies is different for men and women. This is a substantial problem as conventional clinical wisdom suggests that manipulative therapies are often applied to address a “hypo-mobile” or “stiff” vertebral joint. In fact, Brodeur and colleagues reported differences in lumbar stiffness between male subjects with LBP and matched healthy controls.[66] Additionally, a longitudinal study of patients with sub-acute LBP and matched healthy controls found LBP subjects had an 8% decrease in intervertebral stiffness once they became asymptomatic.[67] However, it is unknown if an increase in stiffness at one or more vertebral segments translates to an increase in stiffness in the lumbar spine as a whole. Yet this would be completely consistent with the clinical perspective that manipulative therapies are aimed at reducing stiffness of individual segments (and possibly the trunk as a whole), with the goal of decreasing pain and improving function. In fact, recent findings indicate that trunk stiffness, assessed using a quasi-static method, is increased in subjects with LBP.[68, 69] Furthermore, Hodges and colleagues have recently suggested that an increase in dynamic trunk stiffness observed in subjects with recurrent LBP may, in part, account for the recurrence of LBP symptoms. While trunk stiffness has also been assessed in numerous movement tasks in healthy individuals,[70-72] no published studies have examined the influence of a course of manipulative therapies on trunk stiffness. Further, sex differences in trunk stiffness in the axial and coronal planes has not been examined in patients with chronic LBP patients who fit the clinical prediction rule for manipulation. Accordingly, we seek to examine the effects of sex on 1) trunk stiffness in response to multi-directional seated perturbations in participants with chronic LBP compared to matched healthy controls and 2) changes in trunk stiffness in response to multi-directional seated perturbations in participants with chronic LBP following an initial spinal manipulative treatment and following a 3-week course of treatment.

Passive trunk stiffness in three cardinal planes during unanticipated seated trunk perturbations will be measured in chronic LBP participants enrolled in the RELIEF study (Experiment 2) and a healthy control group (matched for gender, age, height, and weight)- recruited for the sex/gender differences supplement.

**Specific Aim 1.** To examine the effects of sex and chronic LBP on passive trunk stiffness. H1.1. Male participants with chronic LBP will present with increased stiffness compared female participants with chronic LBP. H1.2. Participants with chronic LBP will present with increased stiffness compared healthy controls.

**Specific Aim 2.** To examine sex differences in the effects of spinal manipulation on passive trunk stiffness. H2.1. There are no net sex effects of spinal manipulation on trunk stiffness. H2.2.Both manipulative interventions will decrease passive trunk stiffness as evidenced by the trunk’s initial mechanical response to multi-directional trunk perturbations.

**Specific Aim 3.** To examine the effects of sex and posture on trunk stiffness.

**Specific Aim 4.** To examine the effects of sex and trunk displacement from internally generated trunk perturbations.

### Research Strategy

## SIGNIFICANCE

Low back pain (LBP) is one of the most common reasons for seeking medical care and accounts for over 3.7 million physician visits per year in the United States alone. Ninety percent of adults will experience LBP in their lifetime, 50% will experience recurrent back pain, and 10% will develop chronic pain and related disability.[1, 4, 73, 74] According to the most recent national survey, more than 18 million Americans over the age of 18 years received manipulative therapies in 2007 at a total annual out of pocket cost of 3.9 billion dollars with back pain being the most common clinical complaint of these individuals.[5] While there is growing evidence for the efficacy of manipulative therapies to treat in LBP,[7-11] little is known on the functional biomechanical effects of these treatments. The lack of a mechanistic underpinning hinders acceptance by the wider scientific and health-care communities, and it also limits the development of rational strategies for using manipulative therapies. Further, we could find no published studies that have examined the influence of sex on trunk stiffness in participants with chronic LBP who fit the clinical prediction rule for manipulation or the acute and chronic effects of spinal manipulation on trunk stiffness. Accordingly, this proposed supplement is significant and of high scientific impact because it will provide critical information on the sex and functional biomechanical effects of the most common complementary and alternative therapies (manipulation and mobilization) used to treat LBP. This will provide an ideal expansion of the goals of the RELIEF study described above.

According to the most recent statistics from the U.S. National Health Interview Survey (NHIS), when collapsing across race and ethnicity, approximately 30.0% of women and 24.1% of men reported low back pain in the previous three months. (Summary Health Statistics for U.S. Adults: National Health Interview Survey, 2009, Table 10 [http://www.cdc.gov/nchs/data/series/sr\\_10/sr10\\_249.pdf](http://www.cdc.gov/nchs/data/series/sr_10/sr10_249.pdf)). These national statistics indicate that females account for a significantly greater percentage of cases of LBP compared to males. Thus, a further examination of potential sex differences in mechanisms of, and responses to treatment for LBP is needed.

Over the past decade there has been growing scientific evidence supporting the clinical effectiveness of both manipulation and mobilization therapies in treating LBP.[10-17] While considerable clinical evidence supporting the efficacy of these manual therapies has emerged, little scientific evidence has been offered to explain the effects and mechanisms underlying these treatments or the potential for sex specific differences in these mechanisms. Many scientists and clinicians have long-postulated that manipulative therapies exert influences on the functional biomechanics of the spine.[15, 39, 75-78] However, at present there are few empirical investigations that have examined the role of sex in trunk stiffness or response to manual therapies in patients with chronic LBP. Our **central hypothesis** is that spinal manipulative therapies will increase spine motion and reduce trunk stiffness assessed during to multi-directional seated trunk perturbation tasks and males with chronic LBP will present with greater trunk stiffness compared to females with chronic LBP.

## INNOVATION

Spinal manipulative therapies are applied in response to clinical findings -specifically to address “hypo-mobile” or stiff vertebral segments- and purport to exert influence on biomechanical spine function through modulation of muscle activity and joint range 1). It is unknown how the theoretical neurologic and muscular effects of manipulation influence the “downstream” spine biomechanics during suddenly applied perturbations. The role of sex on trunk stiffness in the three-cardinal planes has not been assessed nor, is it known whether the theoretical neuromuscular effects of manipulation actually influence trunk stiffness the same for male and females. It has recently been suggested that increased trunk stiffness may be an underlying mechanism in recurrent LBP.[69] This recent finding would be consistent with underlying clinical rationale for manipulative treatments that frequently focuses on reducing stiffness. Thus, this research implements the following innovative methodologies to examine the biomechanical effects of spinal manipulation in chronic LBP. Passive trunk stiffness in the three cardinal planes will be modeled using linear second order systems using our custom 3-D spine models. This research represents an innovative addition to a robust paradigm to assess the neuromuscular response of spinal manipulation to better understand the role of sex in one of the most common interventions for LBP.

## APPROACH

**1. Rationale.** Conventional clinical wisdom suggests that manipulative therapies (manipulation and mobilization) are applied to address a “hypo-mobile” or “stiff” vertebral joint. In fact, Brodeur and colleagues reported differences in lumbar stiffness between male subjects with LBP and matched healthy controls.[66] Additionally, a longitudinal study of patients with sub-acute LBP and matched healthy

[figure not shown]

**Figure 1.** Manipulative therapies are typically used to treat the pain and spasm associated with a hypo-mobile spinal segment. However, the effects of manipulative therapies extend beyond the hypo-mobile segment, and likely interact and function to influence neurological, muscular, biomechanical, and psychological factors. The downstream effects could be a change in trunk stiffness that may influence recovery from an episode of LBP. However, it is unknown if spinal manipulation actually changes trunk stiffness (particularly in the axial and coronal planes). More importantly the role of sex in trunk stiffness or sex effects in the response to spinal manipulation treatments is unknown.

of motion [39] (**Figure**

controls found LBP subjects had an 8% decrease in stiffness once they became asymptomatic.[67] However, it is unknown if an increase in stiffness at one or more vertebral segments translates to an increase in stiffness in the lumbar spine as a whole. Yet this would be completely consistent with the clinical perspective that manipulative therapies are aimed at reducing stiffness of individual segments (and possibly the trunk as a whole), with the goal of decreasing pain and improving function. While Gombatto and colleagues found an increase in trunk stiffness in participants with mechanical LBP, it is worth noting that trunk stiffness was determined from the slope of the force-displacement curve in a quasi-static condition. Thus static and not dynamic trunk stiffness was assessed in this cohort.[79] However, Hodges and colleagues have recently suggested that an increase in dynamic trunk stiffness occurs in subjects with recurrent LBP and may, in part, account for the recurrence of LBP symptoms. But this assessment was on asymptomatic participants (i.e., currently pain free, but a history of recurrent LBP) and was restricted to the sagittal plane. While trunk stiffness has also been assessed in numerous movement tasks in healthy individuals,[70-72] no published studies have examined the influence of a course of manipulative therapies on trunk stiffness. While there is recent evidence that sagittal plane trunk stiffness is greater in men compared to women, this has been only assessed in a paradigm that required active trunk co-contraction.[65] This is due, in part, to the use of a system that required a rigid linkage between the actuator and the trunk to assess trunk stiffness. The additional mass of the rigid link system reduces the sensitivity of the system to detect dynamic stiffness in a resting state. A significant advantage of our system to assess trunk stiffness is that light weight non-deformable Kevlar cables are used in place of a rigid linkage (see Figure 2A). This allows the subject to be released following a perturbation so that the actuator system is not part of their response, thereby enabling sex differences in dynamic trunk stiffness to be assessed with greater sensitivity. Further, trunk stiffness in the axial and coronal planes has not been examined in patients with chronic LBP. Interestingly, recent data suggests that males have greater sagittal-plane trunk stiffness compared to females,[65] but females have a higher prevalence of LBP. Thus an underlying mechanism of LBP may be different in males and females, or it could be due to the limitations of the system used to assess trunk stiffness. Accordingly, the proposed aims provide a robust method to determine the effects of sex and spinal manipulative therapies on trunk stiffness in response to multi-directional seated perturbations.

## 2. Assessing Trunk Stiffness

Assessing Trunk Stiffness Using Unpredictable Multi-directional Loads (Sitting): To quantify trunk stiffness in the three cardinal planes, we will use a linear second order system to model trunk stiffness in response to unpredictable multidirectional trunk loading. This methodology has been recently used by Hodges and colleagues to demonstrate that individuals with increased trunk stiffness are at greater risk for chronic and recurrent low back pain.[69] We will use our custom-built apparatus, illustrated in **Figure 2**, to measure stiffness and trunk muscle control patterns during multi-directional trunk loading. For these experiments, the subject is seated with the lumbar spine in a neutral position. The subject's pelvis is securely fastened using seatbelts that cross the mid thighs. A chest harness is snugly attached to the subject at the level of the 3rd thoracic vertebrae. As shown in Figure 2A, non-deformable Kevlar cables (1/4" diameter) are attached the 4 corners of harness by gimbals and run to the corners of the reference frame through a pulley system to attach to actuators set in force control mode. This will allow us to precisely control the load magnitude and duration of the perturbing force pulse. Participants sit in the reference frame with their arms held across their chest. To generate the loading force, the actuators are engaged in pairs (e.g. front, back, left side, right side) to induce a perturbation in one of the following directions: flexion, extension, side-bend left, side-bend right, rotation left, or rotation right. The actuators provide a rapid load pulse of sufficient magnitude to induce 2 inches of trunk displacement in 100-ms. Thus the applied force is proportional to the subject's anthropometric characteristics. Once the impulse load is delivered to the trunk, all 4 Kevlar cables go slack and trunk stiffness is determined from the kinematic responses. The low mass-design of this system will not only allow a simplified mechanical model in evaluating stiffness, but may also be more sensitive than designs that use a rigid linkage between the actuator and the trunk to manipulate the subjects. In this study, the forces will be delivered at random time intervals between 2 and 30 seconds. The onset of the force will

result in a small trunk angular displacement (5-10 degrees) and a long latency postural reflex response of the trunk muscles. In this paradigm, the participant will be exposed to 3 loads in each of the 6 directions listed above. The sequence of the load direction (e.g. flexion, extension, rotation right etc.) will be randomized for each participant.

Once data are collected, system properties of the trunk will be estimated from the time of onset of the perturbing forces until maximal trunk displacement. Effective trunk mass (M), damping (B), and stiffness (K) will be assumed to be constant after the perturbation and will be described by a second-order linear model (Equation 1).

$$F(t) = M * \text{Acceleration}(t) + B * \text{Velocity}(t) + K * \text{Position}(t)$$

$F(t)$  is the resultant force vector on the trunk. The change in trunk position will be measured using the Vicon system. Trunk velocity and acceleration will be determined using a Savitzky-Golay filter. [80] The force applied to the trunk during the perturbation will be measured from the pairs of load cells that are in-series with the actuators. Consistent with the methods proposed by Hodges and colleagues, M, B, and K will be assumed to be constant, and a standard least squares procedure will be used to solve the estimation. The data for the second order linear equation will be integrated numerically twice over time to increase the

[figure not shown]

procedure's robustness.

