Collectively, data from these physiological outcome groups will test the central hypothesis that manual therapies—particularly spinal manipulation techniques— reduce spinal reflex gain (reflected by decreased short-latency reflex response), which in turn decreases reflexive muscle activity (i.e., spasm; reflected by diminished resting MRI T2 signal and surface EMG). The decreased muscle spasm leads to reduced pain, which should remove or reduce inhibitory effects arising from nociceptive afferents projecting to the motor cortex. This leads to an increase in motor cortex excitability (reflected by an increase in intracortical facilitation and/or decrease in intracortical inhibition). Ultimately, when pain and inhibitory input to the motor cortex are reduced, pain and disability decrease and volitional movement is improved. Additionally, the supplemental research data will test the hypothesis that male participants with chronic LBP will present with increased stiffness compared to female participants with chronic LBP, that participants with chronic LBP will present with increased stiffness compared to healthy controls, that there are no net sex effects of spinal manipulation on trunk stiffness, and both manipulative interventions will decrease passive trunk stiffness as evidenced by the trunk's initial mechanical response to multi-directional trunk perturbations.

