  - **Methods:** *In this experimental setup, the subject is seated with the lumbar spine in a neutral position. The subject's pelvis is securely fastened using seatbelts that cross the mid-thigh and across the anterior superior iliac spine. A chest harness is snugly attached to the subject at the level of the 3rd thoracic vertebrae. Kevlar cables (3/16" diameter) are attached to load cells affixed to the 4 corners of harness by gimbals and run to the corners of the reference frame through a pulley system to attach to actuators set in force control mode. This will allow us to precisely control the magnitude of the perturbing force as well as the duration of this pulse. Specifically, the participant will sit in the perturbation reference frame with their arms held across their chest. To generate the perturbing force, the actuators will be engaged in pairs (e.g. front, back, left side, right side) to induce a perturbation in one of the following directions: flexion, extension, side-bend left, side-bend right, rotation left, or rotation right. The actuators will provide a 100-ms duration perturbation force equal to 10% of trunk mass calculated from anthropometrics.[52] The forces will be delivered at random time intervals between 2-30 seconds. The onset of the force will result in a small trunk angular displacement (5-10 degrees) and a long latency postural reflex response of the trunk muscles.*
  - **EMG Data:** Surface EMG electrodes will be placed bilaterally over the muscle belly of the following trunk muscles using double sided tape collars: 1) Erector Spinae at the L2 level aligned parallel to the line between the posterior superior iliac spine (PSIS) and the lateral border of the muscle at the 12th rib, 2) Rectus Abdominis (RA) 1 cm above the

umbilicus and 2 cm lateral to the midline, 3) External Oblique (EO) just below the rib cage along a line connecting the most inferior portion of the costal margin and the contralateral pubic tubercle, and 4) Internal Oblique (IO) 1 cm medial to the anterior superior iliac spine (ASIS) and just beneath a line joining both ASIS. EMG signals will be collected using a 16 channel BioPac MP150 System (bandwidth of 10- 500 Hz). The raw EMG data will be amplified (1k), sampled at 5000 Hz, filtered with a 60 Hz notch filter, and then rectified.

- Specifics regarding supplemental research is included in the appendix.

- Lumbar motion during volitional movement tasks

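### The fitted trunk stiffness K is an effective stiffness that may include reflex stiffness, so it cannot by itself support the supplement's claims about passive stiffness

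*Supplement*

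**What the plan says.** **Derivation.** Appendix, Approach, item 2 (Assessing Trunk Stiffness) fits mass M, damping B and stiffness K by least squares to a second-order linear model: "system properties of the trunk will be estimated from the time of onset of the perturbing forces until maximal trunk displacement". All three are held constant, and nothing in the model represents a reflex.

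**Perturbation.** The appendix describes the pulse thus: "The actuators provide a rapid load pulse of sufficient magnitude to induce 2 inches of trunk displacement in 100-ms". Section 6.2.2 (Baseline Assessments) gives the same duration: "The actuators will provide a 100-ms duration perturbation force equal to 10% of trunk mass". Afterwards, "Once the impulse load is delivered to the trunk, all 4 Kevlar cables go slack and trunk stiffness is determined from the kinematic responses". The appendix expects the force to "result in a small trunk angular displacement (5-10 degrees) and a long latency postural reflex response of the trunk muscles".

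**Label.** Aims 1 and 2, the Innovation paragraph and Section 1.1 call the outcome passive stiffness. H2.2 reads: "Both manipulative interventions will decrease passive trunk stiffness as evidenced by the trunk’s initial mechanical response to multi-directional trunk perturbations". The outcome lists in the Précis and Sections 3, 6.2.4 and 9.4 say dynamic trunk stiffness instead, and the appendix's model paragraph speaks of effective system properties.

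**Reflexes elsewhere.** Section 1.1 hypothesises that manual therapies "reduce spinal reflex gain (reflected by decreased short-latency reflex response"). Trunk EMG is recorded in the perturbation trials, and muscle onset latencies are a separate Experiment 2 outcome. Neither is used to limit the fitting window or to split K.

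**The concern.** A passive property is what the tissue shows before muscle activity responds. H2.2 appeals to the initial mechanical response, but the fit covers the whole outward movement. If reflex force develops before the trunk reaches its peak, a one-K model has nowhere to put it except M, B and K. The estimate then depends on reflex gain as well as on tissue.

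The treatments are themselves hypothesised to act on reflexes. If they change the reflex evoked here, that change differs by arm, so neither randomisation nor the sham arm removes it. H2.2 could be declared supported, or a difference between patients and controls reported under Aim 1, with passive tissue unchanged. The plan offers no way to tell the two explanations apart.

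**Working it through.** The plan states no figure to reproduce. There are two questions: does the window outlast the pulse, and how far could a reflex change move fitted K?

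**1. Inputs.** From the documents: a 100-ms pulse, 2 inches (5.08 cm) at 100 ms, zero force afterwards, and the model F = M·a + B·v + K·x, integrated twice and fitted from onset to peak. The pilot fall in stretch reflex amplitude in Section 9.2 is (0.56 − 0.39)/0.56 = 30%. Assumed, because the documents are silent: M 10-25 kg, B 50-300 N·s/m, K 1000-3000 N/m; a rectangular or half-sine pulse; a total reflex delay (neural plus force build-up) of 30-150 ms; reflex as delayed position feedback of 0.3K or delayed velocity feedback of 0.5B. The model is linear, so percentage changes in K do not depend on pulse size.

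**2. Time to peak.** For an undamped trunk and a symmetric pulse of length T, the displacement peak after the pulse falls at T/2 + π/(2ω), with ω = √(K/M).
- M 10, K 3000: ω = 17.3 per second, peak at 0.050 + 0.091 = 0.141 s.
- M 25, K 1000: ω = 6.3 per second, peak at 0.050 + 0.248 = 0.298 s.

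Damping brings the peak forward. Simulation with damping gives 118-277 ms (median 164 ms), beyond 100 ms in all 54 settings. Reflex force starting within 100 ms of force onset then lies inside the window.

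**3. Effect on fitted K.** Without a reflex the fit recovers the true value (2000 for 2000). With a reflex, medians over the 54 settings are:

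| Total delay | Fitted K above passive K (position / velocity) | Change in fitted K when reflex gain falls 30% (position / velocity) |
|---|---|---|
| 30 ms | 27% / 34% | −6.4% / −8.3% |
| 50 ms | 20% / 54% | −5.0% / −11.7% |
| 80 ms | 8.5% / 33% | −2.2% / −6.9% |
| 100 ms | 3% / 17% | −0.9% / −3.7% |
| 120 ms | 1% / 6% | −0.2% / −1.4% |
| 150 ms | about 0 / 0.2% | about 0 / about 0 |

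The spread across settings is wide. At 80 ms the change runs from −0.3% to −5.2% for position feedback and from −1.6% to −19.8% for velocity feedback. A narrower set of 18 settings (peaks at 142-260 ms) gives falls of about 2-7% at 40-80 ms and under 3% at 120 ms.

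**4. One case in full.** M 15, B 150, passive K 2000, position reflex of 600 N/m delayed by 60 ms. Fitted K is 2344. With reflex gain 30% lower it is 2243. The apparent fall is (2344 − 2243)/2344 = 4.3%, while passive K is 2000 in both.

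**5. Could a shorter window rescue the passive label?** With noise-free data a fit stopped at 60 ms returns 2000 in that case, with or without the reflex. Real data are different. The only stated kinematic specification is 100 Hz and 0.1 mm (Section 6.2.2, for the reaching task), so 60-80 ms holds 7-9 frames for three parameters. With 0.1 mm noise and a true K of 1500, one implementation gave interquartile ranges of about −6600 to 4600 at 60 ms and −1200 to 2000 at 80 ms. Another gave −12514 to 26178 and 1895 to 8986, against 1512 to 1565 for the full window.

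**The case against.** **Overlap is inferred.** The documents state no reflex latency and no time to peak, and the reflex they name is a long-latency one. If reflex force builds up only after about 120 ms, its typical effect is small. The stated 5-10 degree displacement also favours earlier peaks. With an assumed lever of 0.40-0.45 m, two inches is already about 6.5-7.3 degrees, and settings that stay within the stated range generally peak at about 117-165 ms. This stands: a reader might infer that the window certainly contains the reflex, and the documents do not show that.

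**Two reflexes.** A reader might also infer that contamination must favour H2.2. Section 1.1 predicts lower gain of the short-latency reflex, which Section 6.2.2 elicits with a mechanical tap. The perturbation evokes "a long latency postural reflex response of the trunk muscles". For onset latencies after the perturbation, Section 9.1 predicts a treatment effect without a direction. No fall in the long-latency response is stated, so this objection stands too.

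**Benchmark.** It is tempting to compare these figures with the 8% stiffness change cited under Specific Aims. That change is intervertebral, and the same paragraph says it is unknown whether segmental stiffness carries over to the lumbar spine as a whole. The comparison should not be made.

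**Published method and existing labels.** The procedure follows a cited study, and most of the plan already says dynamic or effective stiffness. That supports the estimator. It does not justify calling its K passive in the aims and in H2.2.

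**Conclusion.** The point holds as a mismatch between what is estimated and what is claimed. The fitted K is effective stiffness, and nothing in the plan confines it to the passive part. The mechanism does not depend on the simulation; its size does. If reflex stiffness is 30% of K (an assumption with no source in the documents), a 30% fall in gain moves fitted K by roughly 2-7% at 40-80 ms total delay, and typically by little beyond about 120 ms. Velocity feedback gives larger values. The direction is plausible but not established.

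The consequence is confined to the supplement's stiffness aims, chiefly H2.2 and the reading of H1.2 under Aim 1. The trial's co-primary outcomes and the primary mechanistic hypotheses are untouched.

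**What to change.** 1. In Section 1.1, Specific Aims (Aims 1 and 2, H2.2 and the paragraph introducing them), Innovation, and Hypothesis Testing for Aim 2, replace passive stiffness with effective (dynamic) trunk stiffness. This matches the outcome lists and the appendix's own model paragraph.
2. State that a treatment-related change in K, or a difference between patients and controls, will not be attributed to passive tissue.
3. Optionally, and as exploratory only, report how the change in K relates to the EMG responses recorded in the perturbation trials of participants with low back pain. The documents do not say that EMG is recorded in the healthy controls, so this may not be possible for H1.2.

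Do not make the passive label depend on a fit truncated at EMG onset: K is not reliably estimable from so short a window.

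The cost is a wording change, with no new measurements. The downside is that H2.2 becomes a less specific mechanistic claim.
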